## Abstract

**Background:**

There is considerable evidence from the literature that children with chronic lung disease of infancy (CLD) have abnormal pulmonary function in childhood and this could have an impact on their life quality and overall health. There are similarities between CLD and asthma, and corticosteroids are the mainstay treatment for asthma. Many physicians use inhaled corticosteroids in children with CLD with no evidence. Therefore we wish to conduct a randomized double-blinded placebo controlled trial to test for the role of inhaled corticosteroids in children aged from3 to 9 years with a history of CLD. Our primary hypothesis will be that inhaled corticosteroids are beneficial in children with CLD.

**Methods:**

Our primary hypothesis is that using inhaled steroids; Beclomethasone Dipropionate (QVAR) 100 mcg 2 puffs 2 times a day for 6 weeks will improve the respiratory system resistance and the quality of life in children with CLD.

**Discussion:**

We propose that Beclomethasone Dipropionate (QVAR) will affect the pulmonary function after 6 weeks of treatment. In summary we think that our study will highlight knowledge on whether the use of inhaled steroids is clinically effective for CLD.

## Background

Children with a history of severe CLD were left with significant pulmonary sequelae at school age compared with prematurely born children who had required ventilator assistance and supplemental oxygen in the neonatal period but who did not go on to have CLD [1]. It was also documented that prematurely born children with respiratory distress syndrome (RDS) have long term pulmonary sequelae consisting of airway obstruction and airway hyper reactivity, which are related to both the severity of the initial pulmonary insult and its treatment as well as to a familial predisposition to airway hyper reactivity. The role of inhaled corticosteroids in children with chronic lung disease of infancy or bronchopulmonary dysplasia was not previously studied although most if not all physicians use this treatment for these children whenever they develop chest infections or wheezy episodes. This is a randomized double blinded placebo controlled study using inhaled corticosteroid (CFC free Beclomethasone dipropionate, QVAR) for 6 weeks and measuring the effect on pulmonary function and quality of life.

## Methods

We will use a double blind randomized parallel design. Patients will be invited to the study by sending a letter from the perinatal clinic office inviting them to contact us. Consent will be handed to the parents at the beginning of the study. Subject randomization will be carried out using a computer generated random numbers. Medications and placebo will be kept locked in a cabinet in the clinic area, one of the clinic nurses will be responsible for dispensing the medication or placebo. The medication or placebo will be taken twice daily, at 08:00 and 20:00. The Placebo will have the same taste, shape and color of the study drug. There will be a run in period for 1 week before the study, for teaching the patients, and checking proper technique, and filling out the Child Health Questionnaire (CHQ). In the first visit, informed consent filled, inclusion and exclusion criteria will be obtained. Medical and surgical history, physical exam, inhalation and pulmonary function technique will be done. We will review the daily diary, and prepare the placebo for all patients in the run in period. One week after the run in period, randomization carried out and patients entered into the study. Phone calls will be carried out every two weeks to optimize compliance. After six weeks of treatment, CHQ will be filled. Forced expiratory volume at 1 second (FEV1) (for children older than 6 years of age) and respiratory system resistance at 5 Hz frequencies will be measured.

The Impulse Oscillometry tool to be used is developed by Jaeger Company (Wurzburg, Germany). In short rectangular mechanical impulses containing the whole frequency spectrum are applied to the respiratory system by a mouthpiece, while the patient is breathing quietly. The resulting pressure and volume signals are analysed for their amplitude and phase difference to determine the Rrs at 5 Hz of the total respiratory system [2]. One investigator will perform all pulmonary function tests. After a short explanation, the children will perform some practice trials. When the child is feeling comfortable, a measurement of 25–35 seconds will be started. Patients will be asked to breathe quietly through a round mouthpiece. A nose clip will be used and the cheeks will be supported by the hands of the investigator to minimize pressure loss through the upper airway shunt. Measurement will be discarded if the time-flow pattern showed apnea, speaking, swallowing or air leak, as described by Bisgraaed and Klug. The following parameter Rrs at 5 Hz will be recorded before and 20 minutes after administration of 200 mcg salbutamol. The spacer device used to administer the medication will be an aerochamber with mask for children under the age of 4.7 yrs old and with a mouth piece for children above the age of 4.7 yrs [3-5].

The Study of a patient should be delayed six weeks if developed a viral respiratory illness. Bronchodilators should not be used on the day of the study visit (at least 24 hours for long acting, 6 hours for short acting). Neonatal variables to be collected from medical records: gender, birth weight, birth length, head circumference, gestational age, neonatal treatment, total days on oxygen, maximal FiO2, days on CPAP, days on IPPV, use of steroids (how much and how long), and the use of surfactant. Maternal data: parity, living offspring's, and smoking days during pregnancy. Skin prick testing for the 10 common allergens will be done at the start of the study. Atopy will be defined by one or more positive reactions (3 mm wheal) to 10 common aeroallergens. Parents will fill out daily symptom scores. Social and environmental data to be collected are smoking habits, pets, family history of asthma and asthma in the child. Methacholine challenge testing will be done in the start of the study to define those patients with airway hyper reactivity, which might be a sensitive indicator of response to steroids [6,7]. Respiratory function will be measured using Spirometry (FEV1) and Impulse Oscillometry (RS @ 5 Hz). Quality of life will be measured using the CHQ. Treatment group will receive QVAR 100 mcg 2 puffs twice daily; placebo will be given to the other arm for 6 weeks, after which the respiratory function and quality of life will be measured.

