### Primary hypothesis

Inhaled corticosteroids, Beclomethasone Dipropionate will improve respiratory system resistance after 6 weeks of treatment.

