### Primary outcome measures

Improvement in respiratory system resistance at 5 Hz frequency measured by impulse oscillometry after 6 weeks of inhaled corticosteroids in CLD.

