### Secondary outcome measures

Improvement in Quality of life system score using Child Health Questionnaire (CHQ) and FEV1 response to bronchodilators (Salbutamol) after inhaled corticosteroids treatment for 6 weeks in children with CLD.

The inclusion criteria: children between 3 and 9 years of age with a history of CLD with the following criteria.

1. Premature birth at 36 weeks gestation or less.

2. Clinical and radiological diagnosis of CLD. Patient charts will be reviewed and the x-rays will be reviewed, even if there is no x-ray findings patients will be included if they fulfil the other criteria.

3. Requirement of supplemental oxygen to maintain saturation of 90%, for at least 36 wk corrected gestation.

The exclusion criteria:

1. Cardiovascular disease other than PDA (Patent Ductus Arteriosus)

2. Those with severe neurological disease, developmental delay. Oxygen requirement for respiratory diagnosis other than CLD e.g. congenital diaphragmatic hernia and aspiration. An inability to perform spirometry or IOS, or noncompliance with therapy and those with pneumonia.

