### Statistical consideration

The required number of patients was estimated as n = 74 (37 in each group) and to allow 10% dropout we need 82 patients. The sample size estimation was based on a type I error rate of = .05 and a type II error rate of = 0.20. The improvement in airway resistance at 5 HZ as primary end point was expected to be 15% for the treatment group. The coefficient variation for the impulse oscillometry measurement is 10%. The primary statistical analysis of efficacy data is based on the intention-to-treat patients, who were randomly assigned to treatment and received at least one dose of medication. Baseline characteristics will be compared using descriptive statistics including confidence intervals. Imbalance between the groups on key variables, which might influence the observed outcome, will indicate that an adjusted analysis is necessary using these variables. The differences between airway resistance at 5 HZ response will be tested with a 2-tailed paired test on a significance level of = .05. Analysis of FEV1 improvement will be performed by two-tailed T test (= .05). All tests, except those for CHQ, will be done by SSPS procedures. For CHQ analysis, the differences of sum scores at week 6 after treatment to baseline will be tested by Wilcoxon rank sum test using StatXa.

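### Rrs at 5 Hz is recorded before and after salbutamol, but neither the primary outcome nor the primary test says which reading is analysed, and the paired test defines no between-arm contrast

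*Protocol article*

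**What the plan says.** The oscillometry paragraph in Methods sets two readings of the primary variable: "The following parameter Rrs at 5 Hz will be recorded before and 20 minutes after administration of 200 mcg salbutamol". A session therefore gives a pre-salbutamol value, a post-salbutamol value and their difference.

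The sections that define the primary question do not refer to salbutamol:

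- The endpoint, as worded in the section on primary outcomes, is "Improvement in respiratory system resistance at 5 Hz frequency measured by impulse oscillometry after 6 weeks of inhaled corticosteroids in CLD".
- The hypothesis section likewise says only that "Beclomethasone Dipropionate will improve respiratory system resistance after 6 weeks of treatment".
- Statistical consideration expects a 15% improvement in the treatment group, again with no reading named.
- Statistical consideration, test: "The differences between airway resistance at 5 HZ response will be tested with a 2-tailed paired test on a significance level of = .05".

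Salbutamol appears in an outcome definition only once, under Secondary outcome measures: "FEV1 response to bronchodilators (Salbutamol) after inhaled corticosteroids treatment for 6 weeks in children with CLD". The design in Methods is randomized, double-blind and parallel, with 37 children per group before dropout.

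**The concern.** Two things that should be fixed before unblinding are not fixed.

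The first is the reading. Pre- and post-salbutamol resistance answer different questions, because a reading taken after a bronchodilator has already had some reversible obstruction removed. The article's own Discussion says that most patients with CLD have labile airways and better expiratory flow after a bronchodilator. On that account the two readings should differ in these children, and a steroid effect may be larger in one than in the other.

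The second is the contrast. A paired test compares two values from the same child. In a parallel trial without matching, no treated child is paired with a placebo child, so the sentence does not describe a comparison of the arms.

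What is at stake is the error rate of the only test the trial is sized for, and whether that test uses the randomization at all.

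**Working it through.** **1. Which reading?** Setting the sections side by side:

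| Section | What is named | Pre or post salbutamol? |
|---|---|---|
| Methods, oscillometry paragraph | Rrs at 5 Hz | both recorded |
| Primary hypothesis | resistance after 6 weeks | not stated |
| Primary outcome measures | improvement in resistance after 6 weeks | not stated |
| Statistical consideration, effect size | 15% improvement | not stated |
| Statistical consideration, test | differences in *response*, paired | not stated |

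Methods also requires bronchodilators to be withheld before a visit. This makes a clean pre-salbutamol reading possible, but a salbutamol response needs the same withholding, so it does not settle the choice.

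**2. Does the sample size reveal the reading?** It does not. With a difference of 15 and the stated 10% coefficient of variation used as the SD, two-sided alpha 0.05 and power 0.80:

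n per arm = 2 × [(1.960 + 0.842) × 10 / 15]² = 6.98, so 7.

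The stated figure is 37. For 37 per arm to give 80% power against a 15% difference, the SD would have to be

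15 / [(1.960 + 0.842) × √(2/37)] = about 23%.

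The stated inputs do not reproduce the stated size, which is a separate matter. Here it means only that the calculation cannot be used to infer which reading was intended.

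**3. Which contrast?** The paired test can be taken in two ways:

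- Baseline against week 6 within a child. This tests change within an arm. The placebo arm can also change over six weeks, so a significant change under active treatment is not evidence of a treatment effect.
- Pre- against post-salbutamol within a child. This tests the effect of salbutamol.

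Neither compares the arms. In the same section, the CHQ analysis is spelled out as week-6-minus-baseline differences tested with a rank sum test, which is a between-group test of change. The primary variable has no equally clear sentence.

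**4. Cost of choosing the reading late.** Suppose there is no treatment effect and each reading is compared between arms at two-sided 0.05. Let Z₁ and Z₂ be the test statistics for the pre- and post-salbutamol changes, with correlation r. The chance that at least one is significant is

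P(|Z₁| > 1.96 or |Z₂| > 1.96) = 1 − P(|Z₁| ≤ 1.96 and |Z₂| ≤ 1.96).

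The limits follow directly: r = 1 gives 0.05, and r = 0 gives 1 − 0.95² = 0.0975. In between, by simulation of bivariate normal statistics (2 million draws):

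| Assumed r | P(at least one significant) |
|---|---|
| 0.5 | 0.091 |
| 0.7 | 0.083 |
| 0.8 | 0.078 |
| 0.9 | 0.070 |
| 0.95 | 0.065 |

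The article gives no correlation. Two readings taken 20 minutes apart in the same child should be well correlated, so 0.5 to 0.9 is taken as a plausible range. That gives about 9% down to 7%.

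**The case against.** The strongest reply is that the intended variable is clear enough and that a condensed article may leave the rest to the full protocol or analysis plan. The hypothesis, the outcome and the 15% effect all describe a level of resistance changing over six weeks of steroid. Elsewhere the article uses *response* for response to steroids, so the word in the test sentence most naturally means the six-week treatment response. Where a salbutamol response is wanted, it is named, and only for FEV1. Pre-salbutamol resistance is then the obvious default.

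Much of this stands. A reader might infer that three primary tests are open: pre-salbutamol, post-salbutamol and the salbutamol response. The article does not support that. It plans one primary test, and the salbutamol response is an unlikely primary variable given how the hypothesis and outcome are worded. A reader might also infer that withholding bronchodilators proves a pre-salbutamol endpoint. It does not, for the reason given in the check.

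Two parts of the reply do not stand. Pre-salbutamol may be the natural reading, but both levels fit every primary sentence. And the test sentence is not merely brief: it states a paired test for a parallel-group comparison. That is something the article fixes badly, not a detail left for another document.

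**Conclusion.** The point holds as a defect of definition. As written, the article does not give one valid primary comparison: the reading is unspecified and the stated test is not a between-arm contrast.

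The size is a type I error of about 7% to 9% instead of 5%, conditional on the reading being chosen between pre and post after the data are seen, and on an assumed correlation of 0.9 to 0.5. It is a risk that the wording permits. Nothing in the article says that such a choice is planned.

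A reader might go further and infer a serious loss of power if the post-salbutamol reading were used. The article does not support a figure. The share of the steroid effect that remains after salbutamol is not given, and the standardized effect is unclear: 15/10 = 1.5 from the stated inputs, against about 15/23 = 0.65 implied by 37 per arm. At 1.5, even if only half the effect remained (an assumption), power with 37 per arm would still be about 89%. The case therefore rests on the undefined variable and contrast, not on power.

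**What to change.** In Primary outcome measures, name one variable: pre-salbutamol Rrs at 5 Hz at week 6.

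In Statistical consideration, replace the paired *response* test with a comparison of that variable between the two arms, adjusted for pre-salbutamol baseline Rrs at 5 Hz (analysis of covariance), two-sided at 0.05. An improvement endpoint already needs the baseline value, so the covariate adds no data collection. The pre-salbutamol level is the natural choice because the hypothesis concerns the effect of the steroid on resistance, and this reading is taken before the test dose of salbutamol acts.

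List post-salbutamol Rrs at 5 Hz and the salbutamol response in Rrs as secondary or exploratory.

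The change must be made before unblinding. It costs wording in two sections and needs no added patients, visits or measurements. With one named reading and one contrast, the primary test returns to 5% and no multiplicity allowance is needed in the sample size.

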### Aim of the study

To study the effect of inhaled steroids on school- aged children with CLD.

### Primary hypothesis

Inhaled corticosteroids, Beclomethasone Dipropionate will improve respiratory system resistance after 6 weeks of treatment.

### Primary outcome measures

Improvement in respiratory system resistance at 5 Hz frequency measured by impulse oscillometry after 6 weeks of inhaled corticosteroids in CLD.

### Secondary outcome measures

Improvement in Quality of life system score using Child Health Questionnaire (CHQ) and FEV1 response to bronchodilators (Salbutamol) after inhaled corticosteroids treatment for 6 weeks in children with CLD.

The inclusion criteria: children between 3 and 9 years of age with a history of CLD with the following criteria.

1. Premature birth at 36 weeks gestation or less.

2. Clinical and radiological diagnosis of CLD. Patient charts will be reviewed and the x-rays will be reviewed, even if there is no x-ray findings patients will be included if they fulfil the other criteria.

3. Requirement of supplemental oxygen to maintain saturation of 90%, for at least 36 wk corrected gestation.

The exclusion criteria:

1. Cardiovascular disease other than PDA (Patent Ductus Arteriosus)

2. Those with severe neurological disease, developmental delay. Oxygen requirement for respiratory diagnosis other than CLD e.g. congenital diaphragmatic hernia and aspiration. An inability to perform spirometry or IOS, or noncompliance with therapy and those with pneumonia.

### Statistical consideration

The required number of patients was estimated as n = 74 (37 in each group) and to allow 10% dropout we need 82 patients. The sample size estimation was based on a type I error rate of = .05 and a type II error rate of = 0.20. The improvement in airway resistance at 5 HZ as primary end point was expected to be 15% for the treatment group. The coefficient variation for the impulse oscillometry measurement is 10%. The primary statistical analysis of efficacy data is based on the intention-to-treat patients, who were randomly assigned to treatment and received at least one dose of medication. Baseline characteristics will be compared using descriptive statistics including confidence intervals. Imbalance between the groups on key variables, which might influence the observed outcome, will indicate that an adjusted analysis is necessary using these variables. The differences between airway resistance at 5 HZ response will be tested with a 2-tailed paired test on a significance level of = .05. Analysis of FEV1 improvement will be performed by two-tailed T test (= .05). All tests, except those for CHQ, will be done by SSPS procedures. For CHQ analysis, the differences of sum scores at week 6 after treatment to baseline will be tested by Wilcoxon rank sum test using StatXa.

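### The printed sample-size inputs (15% improvement, 10% coefficient of variation, alpha 0.05, 80% power) do not lead to 37 children per group

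*Protocol article*

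**What the plan says.** Everything the protocol article gives on trial size is in Statistical consideration.

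- Error rates: "The sample size estimation was based on a type I error rate of = .05 and a type II error rate of = 0.20".
- Effect: "The improvement in airway resistance at 5 HZ as primary end point was expected to be 15% for the treatment group".
- Variability: "The coefficient variation for the impulse oscillometry measurement is 10" per cent. This is the only variability figure in the article.
- Result: "The required number of patients was estimated as n = 74 (37 in each group) and to allow 10% dropout we need 82 patients".
- Test of the primary outcome: the difference in resistance response "will be tested with a 2-tailed paired test on a significance level of = .05".

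The Methods section fixes the comparison: "We will use a double blind randomized parallel design". No section gives an SD of change, a change expected on placebo, a within-child correlation or a sample-size formula.

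**The concern.** The paragraph reads as a complete calculation: two error rates, an effect, a variability figure and a resulting size. A 15% effect against 10% variability is a standardised difference of 1.5, which is very large and needs only a handful of children per arm. The stated 37 per group is about four times that, so rounding or a small-sample correction cannot explain it.

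The inputs are also loosely fixed. The 10% is attached to the oscillometry measurement, which may mean repeatability of the device. A comparison of change between arms needs the SD of that change across children. The 15% is attached to the treatment group, whereas the trial tests active against placebo.

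This paragraph is the only justification for the trial's size on its primary endpoint. If its inputs do not produce its result, the claimed 80% power cannot be used to interpret the trial, in particular a null result.

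**Working it through.** **Inputs from the article.** Type I error 0.05, two-sided (as in the stated test); power 0.80, from "a type II error rate of = 0.20"; effect 15%; coefficient of variation 10%; two parallel groups of equal size, "n = 74 (37 in each group".

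**Assumption needed.** No placebo change is stated, so it is taken as zero and the 15% as the between-arm difference.

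**Formula.** Normal approximation: n per group = 2 × (1.960 + 0.842)² × (SD / difference)² = 15.70 × (SD / difference)². The two-sample t-test result comes from the noncentral t distribution.

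**Attempt to reproduce 37, with the 10% as the outcome SD.**
- Standardised difference: 15 / 10 = 1.5.
- Normal approximation: 15.70 / 2.25 = 6.98, so 7 per group.
- t-test: 8.06, so 9 per group (18 in all).
- Power of the t-test with 37 per group: above 99.9%.

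**With the 10% as the repeatability of a single reading.** This assumes that the figure is within-child and that the errors of the baseline and week-6 readings are independent.
- SD of change from measurement error alone: √2 × 10% = 14.1%. Differences between children in response would add to it.
- Standardised difference: 15 / 14.1 = 1.06.
- Normal approximation: 15.70 / 1.125 = 13.95, so 14 per group. t-test: 14.98, so 15 per group.
- Power with 37 per group: 99.4%.

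**Other readings, per group.**

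| Reading | n |
|---|---|
| One-sided test, SD 10% (normal) | 6 |
| 90% power, SD 10% | 10 (normal), 11 (t) |
| 95% power, SD 10% | 12 (normal), 13 (t) |
| Log scale, SD from a 10% coefficient of variation | 6 to 8 |
| Log scale, with the √2 factor | 12 to 16 |
| Paired or one-sample t-test | 6 to 10 |
| Wilcoxon efficiency correction | about 8 to 9 |
| Two proportions, 15% v 0% | 48 (60 with continuity correction) |

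None gives 37.

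**Working back from 37.** The t-test has 80% power with 37 per group at a standardised difference of 0.660. For a 15-point difference the SD is 15 / 0.660 = 22.7% (23.0% by normal approximation). With the SD held at 10%, the difference is 0.660 × 10 = 6.6 points. The article contains neither figure.

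**Power with 37 per group at a 15-point between-arm difference.** All SDs are assumed except 10%, which is the printed figure read as an SD.

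| SD of change | Power |
|---|---|
| 10% | over 99.9% |
| 14.1% | 99.4% |
| 20% | 89% |
| 22.7% | 80% |
| 25% | 72% |

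**The case against.** The best defence is that the 10% was never the SD used. The article says only that the estimate rested on the two error rates. The coefficient of variation comes in a separate sentence and is tied to the measurement. The full protocol may hold the working SD, and a journal article may leave it there. On this view 9 per group is the answer to a calculation that nobody made. Part of this stands: 9 per group holds only if the 10% is the outcome SD, and the √2 step is an assumption too. It does not rescue the paragraph, which prints one effect and one variability figure as the basis of the estimate and a size that follows from neither reading of them.

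Three stronger readings are tempting and are not supported.

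- A reader might infer that the trial is underpowered. On both readings of the 10% the mismatch runs the other way, towards more children than the inputs require. Low power appears only with a larger SD or a placebo improvement that the article does not state. The 15% could also have been meant as an advantage over placebo.
- A reader might infer that about four times too many children are being randomised. That requires 10% to be the true SD of change, which the wording leaves in doubt.
- A reader might count the dropout allowance as a second error. It is not a material one: 74 × 1.1 = 81.4, rounded up to 82, is a common convention, and 74 / 0.9 = 82.2, rounded up to 83, differs by one child.

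**Conclusion.** The point holds as a failure of the stated size to follow from its printed inputs. Those inputs need 9 per group (7 by normal approximation) if the 10% is the outcome SD, or 15 if it is single-reading repeatability, against a stated 37. Both results take the 15% as a between-arm difference with no change on placebo, and the second also assumes independent errors. The 80% power is wrong for the printed inputs. If other inputs were used, it cannot be checked, because a standardised difference of 0.66 is stated nowhere. The type I error is unaffected and the enrolment target need not move, so this should be fixed but does not put the trial's conduct in question.

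**What to change.** Rewrite the sample-size part of Statistical consideration so that its inputs reproduce 37 per group:

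1. Give the effect as a between-arm difference in change in resistance at 5 Hz, and state the change assumed on placebo.
2. Give the SD of that change across children, with its source. Keep it apart from the coefficient of variation of the measurement.
3. Name the two-group test assumed in the calculation. The section currently names a paired test, while Methods describes parallel groups.
4. If 15% and 10% are the true inputs, replace the 80% with the power that 37 per group delivers.

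An SD of 22.7% should not be printed merely because it returns 37. It is back-calculated from the size, and without a source it would justify nothing. Optionally, show power at 37 per group over a range of assumed SDs, as in the last table of the working.

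The cost is one rewritten paragraph. Recruitment need not change.

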Liggins and Howie have demonstrated that the administration of a corticosteroid leads to a decreased incidence of RDS in human premature infants[19]. It is well known that inhaled and systemic steroids are used for the prevention of CLD in infancy [20]. Any pulmonary growth retardation would be expected to have an effect on the airways and result in increased airway resistance and lower flows. It was pointed out that the only major changes in airways from birth to adulthood are in their size [21]. High incidence of asthma has been noted in families of neonates in whom the RDS was complicated by CLD [22]. Other clinical studies suggest an increased incidence of airway hyper reactivity in prematurely born children [23-26]. Recurrent wheeze in childhood and readmission to hospital for bronchiolitis like illness has been observed among prematurely born children who survived the RDS [24]. Most patients with CLD also have increased airway lability and improvement in expiratory flow rates following bronchodilator inhalation suggesting that such therapy may improve pulmonary function in these children [15]. It was anticipated that the incidence of CLD would decrease after the introduction of surfactant therapy, clinical trials by Horbar and Long failed to confirm this [27,28].

So far there are no studies have been published studying the clinical response to inhaled corticosteroids in children CLD. Pulmonary function testing for these children can be done using different techniques. Pennings et al [29] used forced oscillation technique (FOT) to detect changes in airway bronchial tone of asthmatic patients, that were not detected by conventional flow volume recording. It was found that the changes of the diameter of small airways of children could be missed by routine spirometry. The apparent increase incidence of bronchiolitis in RDS survivor's points to these small airways as a source of pathology [30]. In 1956, Dubios et al described the use of FOT as a measure of total respiratory system impedance, which was non invasive and required minimal cooperation from the subject and it can be applied to infants and older children. Laberge et al used FOT to measure respiratory system resistance in 3 to 6 years old asthmatic children and they concluded that the dry powder inhaler (Turbuhaler) and the metered dose inhaler with spacer (Nebuhaler) are equally effective in administering terbutaline [31].

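### Covariate adjustment hinges on observed baseline imbalance, which gives up precision available at no cost and leaves the status of the adjusted result open

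*Protocol article*

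**What the plan says.** In the protocol article, Statistical consideration, baseline data are first summarised by arm: "Baseline characteristics will be compared using descriptive statistics including confidence intervals". The next sentence makes that comparison decide the model: "Imbalance between the groups on key variables, which might influence the observed outcome, will indicate that an adjusted analysis is necessary using these variables". The article does not say which variables are key, what counts as imbalance, or whether the adjusted result supersedes or supports the primary test.

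The primary test itself is stated without covariates: "The differences between airway resistance at 5 HZ response will be tested with a 2-tailed paired test on a significance level of = .05". The endpoint is "Improvement in respiratory system resistance at 5 Hz frequency measured by impulse oscillometry after 6 weeks of inhaled corticosteroids in CLD", which implies a baseline value for every child. Eligible patients are "children between 3 and 9 years of age with a history of CLD". No other section fixes a covariate in advance.

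**The concern.** In a randomised trial, a baseline difference between arms is a chance event and carries no information on whether adjustment is worthwhile. What matters is how strongly the covariate predicts the outcome, and that can be judged before any data are seen. Baseline Rrs5 is the obvious candidate. Age is a reasonable second one across a 3-to-9-year range.

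Under the stated rule these variables enter the model only when they happen to differ between arms. In most trials they would not, so the precision they offer would go unused. The rule also leaves it unclear which analysis is primary once an imbalance has been noted.

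**Working it through.** **Inputs from the article (Statistical consideration).** 37 children per arm; two-sided alpha 0.05 and 80% power ("The sample size estimation was based on a type I error rate of = .05 and a type II error rate of = 0.20"); effect ("The improvement in airway resistance at 5 HZ as primary end point was expected to be 15% for the treatment group"); coefficient of variation 10%.

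**Inputs not in the article, assumed here.** The baseline to week-6 correlation rho (range 0.3 to 0.7); equal variance at both visits; a trigger at p<0.05 on the baseline comparison; and the primary response read as change in Rrs5 compared between arms.

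1. **The plan's own figure.** n per arm = 2 × (1.960 + 0.842)² × (SD/difference)². With 15 and 10: 2 × 7.85 × 0.444 = 7 per arm, not 37. One-sided testing, 90% power, an SD of 10√2, a log scale and a paired calculation do not give 37 either. For 37 per arm to give 80% power at a 15-point difference, the SD must be 15 / (2.802 × √(2/37)) = 23.0. The comparison below uses that SD, so 80% starting power is a premise. With SD 10, power at 37 per arm exceeds 99.9%.

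2. **Precision gain from baseline.** Change-score variance is 2σ²(1 − rho). ANCOVA variance is σ²(1 − rho²). The ratio is (1 + rho)/2, or 0.75 at rho 0.5 and 0.85 at rho 0.7. The same precision from a change score would need 1/0.75 = 1.33 to 1/0.85 = 1.18 times as many patients.

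3. **Power.** ANCOVA power = Φ(2.802/√ratio − 1.960). At rho 0.5: 2.802/0.866 − 1.960 = 1.275, giving 89.9%. At rho 0.7: 2.802/0.922 − 1.960 = 1.079, giving 86.0%.

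4. **Simulation.** 37 per arm, 40,000 trials per scenario, baseline Rrs5 as the only covariate:

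| Assumed rho | Power, change score | Power, ANCOVA fixed in advance | Power, ANCOVA only if baseline p<0.05 | Type I error, triggered rule |
|---|---|---|---|---|
| 0.3 | 79.0% | 92.6% | 80.4% | 3.9% |
| 0.5 | 79.1% | 88.8% | 80.1% | 4.3% |
| 0.7 | 79.3% | 84.8% | 79.7% | 4.7% |

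The trigger fires in about 5% of trials, so the triggered rule recovers little of the gain. Simulated powers sit about a point below the formula, which uses the normal rather than the t distribution.

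5. **If the response were week-6 Rrs5 alone.** The ratio is 1 − rho², and the formula gives ANCOVA power of 83.6%, 89.9% and 97.5% at rho 0.3, 0.5 and 0.7. The direction is the same.

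6. **Several covariates.** The Methods list about 20 baseline items. If each were judged at 5% and all were independent (both assumptions), at least one would look imbalanced with probability 1 − 0.95²⁰ = 64%, or 40% for ten items. Most such triggers would bring in some variable other than baseline Rrs5. With all imbalanced covariates entered and the adjusted result replacing the unadjusted one, simulated type I error (8,000 null trials per scenario) was 3.0% to 4.5% for 8 covariates and 3.6% to 3.9% for 20.

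**The case against.** The strongest reply is that the rule does little harm, and much of it stands.

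- A reader might infer that the primary p-value loses its error control. The documents do not support that. The trigger looks at baseline data, not outcomes, and steps 4 and 6 put its type I error at or below 5%. Inflation needs discretion with outcomes in view. Reporting the better of the unadjusted and the always-available ANCOVA result would give 6.4% to 8.4%; the better of the unadjusted and the triggered result, 5.1% to 6.3%; the best of ten models, about 12%. The article prescribes none of these.
- A reader might infer that the primary model is to be chosen after seeing the data. The article names a primary test and never says an adjusted analysis replaces it. A supportive reading is possible. Because the article calls adjustment necessary, though, the status is unclear.
- Baseline Rrs5 is not ignored. On a change-score reading it already enters, and stable differences in body size largely cancel within a child over six weeks. The Discussion's remark that "the only major changes in airways from birth to adulthood are in their size" concerns growth over life, not differences between trial children, so it is weak support for a size covariate.
- The rule is not blind to prognosis: it is limited to variables that could affect the outcome. It still requires imbalance before such a variable is used.
- A condensed article may leave covariate names and thresholds to a fuller document. That answers the missing detail but not the rule, which is stated here. A later plan would have to follow it or contradict it.

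**Conclusion.** The point holds as one of efficiency and clarity. The direction is firm: on the equal-variance model, ANCOVA with baseline is more precise than a change score for any rho below 1, and an imbalance trigger forgoes nearly all of that gain. The size is conditional. For rho 0.5 to 0.7, 80% power becomes about 90% to 86%, against about 80% under the triggered rule. This rests on an assumed rho, a p<0.05 trigger on a single covariate, and 80% starting power, which the stated 15% effect and 10% coefficient of variation do not reproduce. If those two figures did describe the response, power would already be near 100% and little would be gained. A looser trigger would recover more of the gain. What age adds beyond baseline Rrs5 was not quantified.

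No inflation of type I error follows from the rule as written. The sentence is worth changing, but it does not threaten the validity of the trial.

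**What to change.** Replace the sentence on imbalance with:

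> The primary analysis is ANCOVA of week-6 Rrs5 on treatment, baseline Rrs5 and age, regardless of observed balance. Baseline comparisons are descriptive and do not determine the model. Any further adjusted analysis is a sensitivity analysis.

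Apply the same rule to FEV1 with its own baseline value. Name age rather than height, since current height is not among the listed data. As the Methods record Rrs5 both before and after salbutamol, use the same one of the two at both visits.

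The cost is a change of wording. Improvement in Rrs5 already requires a baseline value, and age is checked at eligibility, so no new data are needed.
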